### Data, monitoring and analysis

#### Data collection and management

Data collection and skin assessments are undertaken by trained staff at the recruiting hospitals. Participants who do not attend clinic visits at 3 or 6 months continue to be invited to subsequent follow-up visits unless they decline further participation in the trial. Every effort is made to ensure the 9-month follow-up visit takes place, and if a face-to-face visit cannot be arranged, data are collected via telephone or email if possible. Data captured at clinic visits are entered by site staff into the web-based trial database.

The year-long follow-up after treatment is by self-completed questionnaires, either via an email link to the trial online system or by post, sent with a stamped addressed envelope. Reminders are sent (via email or post) if the questionnaire remains uncompleted after 2 weeks, and again after 3 weeks. The trial coordinating centre also then chases up outstanding questionnaires after 3 weeks via telephone.

Detailed data management processes and central and on-site monitoring procedures are documented in a data management plan. All sites are monitored at least once after the first five randomisations from that site, and triggered monitoring visits are undertaken if any concerns about the site are raised. Database validation checks are conducted centrally including checks for missing data, out of range values, illogical entries and invalid responses. Data entered by sites into the trial database are subject to monitoring and review by coordinating centre staff, and data queries are raised as necessary. All receive at least one site monitoring visit during the trial.

#### Trial management

Management of the trial is the responsibility of the Trial Management Group, which meets regularly, usually monthly, throughout the trial. Data collection, adherence and retention rates are monitored by this group. Trial oversight is by the independent Trial Steering Committee. Unblinded trial data are monitored in confidence by the independent Data Monitoring Committee, which reports to the Trial Steering Committee. Both oversight committees meet at least annually. The composition of both oversight committees and their charters can be found on the trial website.

#### Sample size

Our choice of minimum clinically important difference between the groups has been informed by a survey of the clinical membership of the UK Dermatology Clinical Trials Network. Assuming that topical corticosteroid alone results in 15% treatment success at 9 months,^12^ clinicians were keen to see at least a 20% absolute difference between the groups if they were to justify the cost and complexity of introducing home-based NB-UVB as a potential new service in clinical practice (either on its own or in combination with topical corticosteroid).

The following sample size estimate formed the basis of the funding application and protocol at the start of the study: based on the assumption that 15% of participants allocated to receive topical corticosteroid alone achieve treatment success,^12^ 372 participants are required to detect an absolute difference of 20%, with 2.5% two-sided alpha and 90% power. Two comparisons are of coprimary interest, light therapy and light therapy plus topical corticosteroid each versus topical corticosteroid alone. Allowing for up to 15% non-collection of primary outcome data at 9 months, the target sample size was 440 participants.

As data were limited to inform the sample size calculation for this trial, a planned sample size review by the Data Monitoring Committee was scheduled after 18 months of recruitment. This review was conducted in December 2016 and resulted in a recommendation to increase the sample size by a further 76 participants in order to maintain 90% power to detect a risk difference of 20% between the topical corticosteroid arm and the other two arms. The final sample size estimate is therefore 516 participants. This recommendation was approved by the Trial Steering Committee and the funders.

#### Statistical methods

The primary approach to between-group comparisons will be to analyse participants according to the group to which they were allocated, regardless of treatment received, levels of adherence and with multiple imputation of missing outcome data.

Baseline data will be presented descriptively, and presented by intervention group.

For the primary outcome, number and percentage of participants achieving ‘treatment success’ will be reported for each treatment group at 9 months from randomisation. Randomised groups will be compared using a generalised linear model for binary outcome adjusted by centre, body site of vitiligo and age. The primary effectiveness parameter for the two coprimary comparisons of topical corticosteroid versus NB-UVB light, and topical corticosteroid versus NB-UVB light plus topical corticosteroid, will be the risk difference in the proportion of participants achieving treatment success at 9 months, along with 95% CI and exact P value. We will also report relative effects using risk ratios. Sensitivity analyses will be conducted to (i) further adjust for any variables with marked imbalance at baseline, (ii)repeat primary analysis based on participants whose primary outcome is available at 9 months and (iii) investigate the effects of treatment adherence. Planned subgroup analyses are (i) children versus adults and (ii) by body region of the target vitiligo patch. Further secondary analyses will be defined in the statistical analysis plan prior to locking the trial database. These analyses will be conducted by inclusion of appropriate interaction terms in the regression model, and will be considered as exploratory.

Analyses investigating other follow-up times, treatment success of patches on other body sites and other secondary outcomes will be analysed by a similar approach, using appropriate regression modelling depending on outcome type.

All analyses will be specified in a statistical analysis plan to be finalised and approved by the Data Monitoring Committee and Trial Steering Committee prior to locking the database.

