### Randomisation and blinding

Participants are randomised to one of three treatment groups in a ratio of 1:1:1 as follows:Topical corticosteroid ointment plus dummy NB-UVB light (corticosteroid only);Vehicle ointment plus NB-UVB light (light therapy only);Topical corticosteroid ointment plus NB-UVB light (combination therapy).

Randomised allocation to treatment groups is minimised by recruiting centre, body region of target patch (face and neck, hands and feet or rest of the body) and age (5–16 years or >16 years), weighted towards minimising the imbalance in trial arms with a probability of 0.8. After all eligibility criteria have been confirmed and medical photographs taken, participants are randomised by staff at the recruiting hospital via a secure web server created and maintained by the Nottingham Clinical Trials Unit.

Participants are only randomised into the trial once they have completed the training in use of the trial interventions, the results of the MED test are known and the participant has attended medical photography for their baseline digital photograph.

Participants, research nurses, principal investigators, members of trial management group and data analysts are blinded to treatment allocation. Only the Nottingham Clinical Trials Unit (NCTU) programmer, the medical physics staff, pharmacy staff and the NCTU Quality Assurance staff have access to the treatment allocation schedule for the sole use of preparing, blinding and checking of the trial treatments.

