#### Interim analyses

There are no planned interim between-group analyses.

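### The two coprimary comparisons are sized at 2.5% two-sided but reported with 95% CIs, so the stated interval does not match the design test

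*Protocol article*

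**What the plan says.** Under Sample size, the protocol article states that "372 participants are required to detect an absolute difference of 20%, with 2.5% two-sided alpha and 90% power". The control rate behind this is that "15% of participants allocated to receive topical corticosteroid alone achieve treatment success". The next sentence gives the structure of the primary question: "Two comparisons are of coprimary interest, light therapy and light therapy plus topical corticosteroid each versus topical corticosteroid alone". Allocation is equal across three arms (Randomisation and blinding). After a sample size review the target was raised: "The final sample size estimate is therefore 516 participants". The account of that review neither restates nor withdraws the 2.5% level.

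Under Statistical methods, the primary effectiveness parameter for these same two comparisons "will be the risk difference in the proportion of participants achieving treatment success at 9 months, along with 95% CI and exact P value". That section gives no significance level, no 97.5% interval and no multiplicity rule. It defers the specification of all analyses to a statistical analysis plan, to be approved before the database is locked. On interim looks the article says: "There are no planned interim between-group analyses".

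**The concern.** A confidence interval and a test agree only when their levels agree. A 95% CI is the set of differences that a 5% two-sided test would not reject. The trial was sized for a 2.5% two-sided test of each comparison, and the matching interval is 97.5%. By fixing 95%, the analysis section presents each coprimary result on a scale that differs from the one the design paid for, and it does not tell the reader which level decides.

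This matters because the two comparisons are alternative routes to a positive trial. According to the Sample size section, clinicians would consider a home NB-UVB service if light worked either alone or together with corticosteroid. With two chances of a positive finding, the error rate over the pair is the relevant quantity, and the 2.5% level keeps it below 5%. If the level is not restated where the analysis is defined, a result between the two thresholds could be called positive or negative after the P values are known.

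**Working it through.** **Inputs.** Success 15% in the control arm and 35% in each comparator (a 20-point difference), 90% power and alpha 2.5% two-sided (Sample size); 1:1:1 allocation (Randomisation and blinding); 15% loss of primary outcome data and 516 participants (Sample size); 95% CI (Statistical methods).

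**Step 1: reproduce the plan's own figure.** Two-proportion formula per arm, mean proportion 0.25:

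n = [z(α/2)·√(2 × 0.25 × 0.75) + z(power)·√(0.15 × 0.85 + 0.35 × 0.65)]² / 0.20²

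Continuity correction: n′ = (n/4)·[1 + √(1 + 4/(n × 0.20))]²

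- α = 0.025: z = 2.241, n = 114.1, n′ = 123.9, so 124 per arm and 3 × 124 = **372**, as stated.
- α = 0.05: z = 1.960, n = 96.4, n′ = 106.2, so 107 per arm and 3 × 107 = 321.

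Without the continuity correction the three-arm totals are 345 (2.5%) and 291 (5%); with unpooled variance they are 333 and 282. Of the variants tried, only 2.5% with the correction gives 372. Then 372/0.85 = 437.6, or 438, close to the stated 440. The 2.5% level is therefore a real design input. Within the same formula it accounts for 372 − 321 = 51 evaluable participants.

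**Step 2: error rate over the two comparisons.** With equal arms and a shared control, the two test statistics have correlation 0.5 under the null. The chance of at least one false finding is 1 − P(|Z₁| < c and |Z₂| < c), from the bivariate normal distribution.

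| Each comparison judged at | c | At least one false finding, either direction | At least one favouring light or combination |
|---|---|---|---|
| 5% (95% CI) | 1.960 | 1 − 0.9093 = 9.1% | 4.5% |
| 2.5% (97.5% CI) | 2.241 | 1 − 0.9535 = 4.6% | 2.3% |

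Treating the comparisons as independent gives upper figures of 1 − 0.95² = 9.75% and 1 − 0.975² = 4.94%. Binomial simulation (500,000 trials per setting; 124, 146 and 172 per arm; common success rates 15%, 25% and 35%) gave 9.0–9.3% and 4.5–4.7%. No interim between-group look is planned, so nothing is added for that.

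**Step 3: width of the intervals.** Take 516/3 = 172 per arm, less 15% loss, which is 146 with observed outcomes. At 15% v 35%:

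SE = √[(0.1275 + 0.2275)/146] = 0.0493

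- 95%: 1.960 × 0.0493 = 9.7 points
- 97.5%: 2.241 × 0.0493 = 11.1 points

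The ratio is 2.241/1.960 = 1.14. If multiple imputation recovered the full information of 172 per arm, SE = √(0.355/172) = 0.0454 and the half-widths would be 8.9 and 10.2 points; the ratio is unchanged.

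**Step 4: an illustration of the gap.** Suppose, as an assumption, that 15% v 25% is observed with 146 per arm. SE = √[(0.1275 + 0.1875)/146] = 0.0464, z = 0.10/0.0464 = 2.15 and P = 0.031. The 95% CI is 0.9 to 19.1 points and excludes zero. The 97.5% CI is −0.4 to 20.4 points and does not. The same data are positive by the reported interval and negative at the design level.

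**The case against.** The strongest reply is that the article fixes a reporting format and not a decision rule. It nowhere says that success will be judged at 5%. The P value is reported too and can be compared directly with the 2.5% in the Sample size section. A reader might infer from the 95% CI that the trial's error rate simply is 9%; the documents do not support that. The figure holds only if success is read from the 95% interval or from P < 0.05. It also counts errors in both directions, and for false claims in favour of light or combination the figure is 4.5%. This part of the objection stands.

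A reader might also infer that the 95% intervals are invalid or too narrow. They are not: each has its nominal coverage for its own comparison, and the article claims no simultaneous coverage. Nor does it name a Bonferroni split; that is an inference, though a natural one from 2.5% and two comparisons.

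It can further be said that the threshold belongs in the unseen analysis plan or full protocol. This is fair for a threshold that is merely absent. But the interval level is not left open: 95% is stated for the same comparisons that were sized at 2.5%. The article's amendment table also records that the statistical section was updated at version 5.0 to agree with the analysis plan, so it cannot be presumed that the plan says something else.

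Finally, the practical reach is limited. With the SE of 0.0493, the two rules disagree only for observed differences of about 9.7 to 11.1 points, roughly half the 20 points that clinicians wanted. That lowers the severity but does not remove the mismatch.

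**Conclusion.** The point holds as a moderate consistency error. The design level is 2.5% two-sided per comparison, confirmed by exact reproduction of 372; the stated interval is 95%; and the analysis section does not say which governs. Results with P between 0.025 and 0.05 are left ambiguous. If the 95% CI or P < 0.05 is used to decide, the error rate over the two comparisons is about 9.1% instead of about 4.6% (4.5% instead of 2.3% for false findings favouring light or combination).

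These rates assume that neither comparator differs from corticosteroid, that arms are equal in size and that the normal approximation holds, which the simulation supports. The interval widths assume 15% v 35%, the planned 15% loss carried over to the 516 target, and no covariate adjustment. The finding does not show that the investigators intend to judge at 5%.

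**What to change.** In the Statistical methods section and in the analysis plan, before database lock, state that each of the two coprimary comparisons is judged at 2.5% two-sided, and give the matching 97.5% CI for each risk difference. The 95% CIs may be kept as supplementary for these two comparisons and as the standard for secondary outcomes. Stating the 0.025 threshold beside the 95% CIs would also control the error, but it would leave intervals that can disagree with the test.

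The cost is a sentence in each document and coprimary intervals about 14% wider (half-width about 11.1 instead of 9.7 points at 146 per arm). No extra participants are needed, because the sample size was calculated at this level.

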#### Interim analyses

There are no planned interim between-group analyses.

### Health economic evaluation

An incremental cost analysis will be conducted from an NHS perspective capturing the intervention resource use and other health resource use throughout the treatment and follow-up period (21 months in total). In addition to an NHS perspective, but presented separately, an estimate of out-of-pocket and time costs of treatment for participants and parents/guardians will be recorded. Intervention and wider healthcare costs will be estimated during the trial through participant dairies and case report forms (CRFs). Resource use will be valued using published unit costs or participant-reported estimates for a common price year. Both costs and benefits will be discounted using recommended rates.^32^

Both an incremental cost-effectiveness analysis using the trial primary outcome to estimate the incremental cost per successful treatment and cost-utility analysis estimating incremental cost per quality-adjusted life years (QALY) will be conducted. Utility will be measured at baseline, 9 months and 21 months using the EQ-5D-5L^26–28^ (for adults and children aged 11 years or over) and CHU-9D^28–31^ (for children aged 5–17 years) questionnaires, which will be used to estimate the QALY over the study period using linear interpolation and area under the curve analysis with and without baseline adjustment.^33^ In the base case, separate cost utility analyses will be presented for those aged 18 years and over using the EQ-5D-5L to estimate QALYs and for those aged under 18 years using the CHU-9D. Where appropriate (ie, in the absence of either intervention dominating), the incremental cost-effectiveness of NB-UVB alone compared with TCS alone and separately of NB-UVB plus TCS compared with TCS alone will be estimated by dividing the difference in costs by the difference in QALYs. Decision uncertainty will be presented via Cost-Effectiveness Acceptability Curves based on non-parametric bootstrapping of cost and effect pairs.^34 35^ This will provide robust trial evidence to inform decision makers about the likely cost-effectiveness of interventions for vitiligo in particular about whether NB-UVB light is more cost-effective than topical corticosteroid alone and about whether combination treatment offers greater value for money than TCS treatment alone.

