There is some evidence to suggest that starting vitiligo treatment when lesions first appear is likely to result in better treatment response, when vitiligo patches are actively changing and some melanin is still present.^14^ However, current practice is to reserve NB-UVB treatment for patients with widespread and established vitiligo,^8^ as the treatment requires thrice weekly visits to the hospital for full body light therapy. The recent availability of hand-held NB-UVB units for private purchase on the open market means that early intervention using treatment at home is now a possibility. Benefits of home-based treatment, if shown to be safe and effective, would be a reduction in time and financial burden for patients and hospital services, and reduced exposure of healthy skin to NB-UVB light as treatment can be targeted more effectively. Our small pilot RCT, involving 29 participants, compared hand-held NB-UVB with dummy devices for the management of vitiligo.^15^ This pilot demonstrated that people with vitiligo were keen to use home-based light therapy, and that the devices were safe and well tolerated when used in a domestic setting.

A James Lind Alliance Priority Setting Partnership identified a ‘top 10’ list of priority areas for vitiligo research that are important to people with vitiligo and healthcare professionals responsible for their care.^16^ Two of these prioritised areas relate to the use of light therapy for the management of vitiligo: ‘Which treatment is more effective for vitiligo: steroid creams/ointments or light therapy?’ and ‘How effective is UVB therapy when combined with creams or ointments in treating vitiligo?’ The prioritisation work was shared with the NIHR Health Technology Assessment Programme who subsequently invited applications to address these two priority topics in open competition. The contract to conduct the commissioning brief was awarded to this team.

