### Objectives

Primary objective:To evaluate the comparative safety and effectiveness of home-based interventions (potent topical corticosteroids and hand-held NB-UVB light) for the management of early and limited vitiligo in adults and children. Specifically, we are comparing:Potent topical corticosteroid (mometasone furoate 0.1% ointment) with hand-held NB-UVB light;Potent topical corticosteroid (mometasone furoate 0.1% ointment) with combination of hand-held NB-UVB light and potent topical corticosteroid.

Secondary objectives:To assess whether treatment response (if any) is maintained once the intervention is stopped.To compare the cost-effectiveness of the interventions from a National Health Service (NHS) and a family perspective.

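### The cost-utility analysis names ratios only against corticosteroid alone, so those ratios do not show whether combination therapy is worth its extra cost over light therapy alone

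*Protocol article*

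**What the plan says.** The trial has three arms: corticosteroid (TCS) with a dummy light, NB-UVB light with vehicle, and both active treatments. Under Randomisation and blinding, "Participants are randomised to one of three treatment groups in a ratio of 1:1:1", so each participant follows exactly one strategy. A secondary objective reads "To compare the cost-effectiveness of the interventions from a National Health Service (NHS) and a family perspective".

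The Health economic evaluation section then fixes the cost-utility contrasts: "the incremental cost-effectiveness of NB-UVB alone compared with TCS alone and separately of NB-UVB plus TCS compared with TCS alone will be estimated", each obtained "by dividing the difference in costs by the difference in QALYs". The ratios are to be computed where neither intervention dominates, which reads as a check within each pair. The section closes with two questions for decision makers. One is whether light is more cost-effective than corticosteroid alone. The other is "whether combination treatment offers greater value for money than TCS treatment alone".

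Two further sentences are less specific. A cost-effectiveness analysis is planned "using the trial primary outcome to estimate the incremental cost per successful treatment", with no arms named. For uncertainty, "Decision uncertainty will be presented via Cost-Effectiveness Acceptability Curves based on non-parametric bootstrapping of cost and effect pairs", without saying whether each curve covers two arms or all three.

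The article nowhere plans combination versus light alone, a ranking of the three arms, or a check for extended dominance.

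**The concern.** When a payer must choose one of several exclusive options, the relevant ratio for each is its extra cost over its extra effect against the next less costly option still in contention. A ratio against a common baseline blends two steps for combination therapy: from corticosteroid to light, and from light to combination. If the first step brings most of the benefit, the blended ratio can look acceptable even when the second step buys very little.

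A decision maker prepared to fund home light therapy would next ask whether adding corticosteroid to it is worth the cost. Neither the named ratios nor the closing questions address that. Because the article states its contrasts explicitly, this is an incomplete stated method and not a detail left to a fuller document.

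**Working it through.** **Inputs.** The three arms and two contrasts come from the article. Its economic section gives no numerical result to reproduce, and no arm costs, QALYs or threshold. All such values below are assumed, including 20,000 pounds per QALY as the threshold.

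**Formulas.** ICER = (difference in cost) / (difference in QALYs). Net monetary benefit (NMB) = threshold × QALYs − cost.

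**Main illustration.** TCS, light and combination cost 100, 500 and 650 pounds and yield 1.300, 1.330 and 1.332 QALYs.
- Light vs TCS (planned): (500 − 100) / (1.330 − 1.300) = 400 / 0.030 = 13,333 per QALY.
- Combination vs TCS (planned): (650 − 100) / (1.332 − 1.300) = 550 / 0.032 = 17,188 per QALY.
- Combination vs light (not planned): (650 − 500) / (1.332 − 1.330) = 150 / 0.002 = 75,000 per QALY.
- NMB: TCS 26,000 − 100 = 25,900; light 26,600 − 500 = 26,100; combination 26,640 − 650 = 25,990.

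Both planned ratios are under 20,000, yet light alone has the highest net benefit.

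**Where this example reverses.** At the same costs, combination vs light equals 20,000 when the added gain is 150 / 20,000 = 0.0075 QALY. Above that gain, combination is preferred.

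**Range on a second set of assumed values.** Costs are 100, 700 and 800 pounds. Light gains 0.040 QALY over TCS, so light vs TCS is 600 / 0.040 = 15,000. Only the gain of combination over TCS varies:

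| Combination gain | Combination vs TCS (planned) | Combination vs light (not planned) | Best at 20,000 |
|---|---|---|---|
| 0.039 | 700 / 0.039 = 17,949 | dearer by 100 and less effective: dominated | light |
| 0.0425 | 700 / 0.0425 = 16,471 | 100 / 0.0025 = 40,000 | light |
| 0.050 | 700 / 0.050 = 14,000 | 100 / 0.010 = 10,000 | combination |

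In all three rows both planned ratios are below the threshold, while combination goes from dominated to best.

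**Extended dominance.** With costs of 100, 700 and 760 and gains of 0.020 (light) and 0.050 (combination), light vs TCS is 600 / 0.020 = 30,000, combination vs TCS is 660 / 0.050 = 13,200, and combination vs light is 60 / 0.030 = 2,000. Light is extendedly dominated. The two planned ratios hint at this, but only to a reader who also knows that combination is both the dearer and the more effective option.

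**Cost per success.** Take costs of 100, 700 and 800, success of 15% and 35% for TCS and light (the sample size section's 15% plus 20 points), and an assumed 36% for combination. Light vs TCS is 600 / 0.20 = 3,000, combination vs TCS is 700 / 0.21 = 3,333, and combination vs light is 100 / 0.01 = 10,000.

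**The case against.** The strongest defence is coherence. The primary objective lists two specific comparisons, both against corticosteroid, and the Sample size and Statistical methods sections make the same two coprimary. The Sample size section frames the decision as whether to introduce home light at all, alone or in combination. The economic section follows that structure. The research priority cited in the Introduction, "How effective is UVB therapy when combined with creams or ointments in treating vitiligo", concerns effectiveness and names no comparator, so it does not itself call for the missing contrast. This explains the choice. It does not make two contrasts sufficient for choosing among three exclusive options under an objective to compare the interventions.

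Four stronger readings might be inferred, and the article does not support them:

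- *That the analysis cannot identify the best option.* Both contrasts share a comparator. If cost and QALY differences are reported, subtraction gives the third: 550 − 400 = 150 and 0.032 − 0.030 = 0.002. Incremental net benefit against TCS also ranks the arms: 0.030 × 20,000 − 400 = 200 for light and 0.032 × 20,000 − 550 = 90 for combination. The section separately plans an incremental cost analysis, so these differences may well be published. Subtraction does not give the uncertainty of the step.
- *That the acceptability curves compare only two arms at a time.* The pairs that the article mentions are a cost with an effect, not one arm with another. A three-arm curve fits that wording and would partly meet the point.
- *That cost per success is limited to the same two contrasts.* That sentence names no arms.
- *That 75,000 against 17,188 measures an error.* No result has been reported, and other assumed values reverse the conclusion.

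It is also fair that combination versus light may be imprecise. The sample size was set for the corticosteroid contrasts, and the base-case cost-utility analysis is split at age 18. That is a reason to show the uncertainty, not to omit the step.

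**Conclusion.** The concern holds in a limited form. The named cost-utility ratios, and the closing value question for combination, all refer to corticosteroid alone. Taken by themselves they do not show whether combination is worth its extra cost over light or whether a light option is dominated or extendedly dominated, and they carry no uncertainty for that step.

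The size is unknown. On assumed values the missing ratio is 75,000 per QALY beside planned ratios of 13,333 and 17,188. On others it is 10,000 and combination is best. The conclusion that the planned ratios are incomplete rests only on the three options being exclusive and on the contrasts that the article states. The primary clinical result is unaffected. A stated secondary objective is only partly served, so this should be corrected but does not threaten the trial.

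**What to change.** Replace the sentence naming the two ratios with a fully incremental analysis of all three arms:

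1. Rank the arms by mean cost, remove dominated and extendedly dominated options, and report each remaining option's ICER against the next less costly remaining one. Do this within each of the two age groups of the base case.
2. Report mean costs, mean QALYs and net monetary benefit by arm, and show the combination-versus-light difference with its uncertainty.
3. Bootstrap the three arms jointly, and state that the acceptability curves show the probability that each of the three options is the most cost-effective.
4. Use the same approach for cost per successful treatment.
5. Keep the two comparisons with corticosteroid as supporting results, and add the choice among all three options to the closing questions.

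The cost is revised wording and a few lines of analysis code, with no new data. The Statistical methods section places approval of the analysis plan before database lock, so the change can be made there. The downside is a little more analysis and a combination-versus-light estimate that may be imprecise, which the text should say.
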